## Feasibility/piloting

### Sub-study III: monocentric interrupted time series (ITS) pilot study

We will conduct a monocentric pilot study. This pilot study will be performed following a pragmatic trial approach to increase applicability to the German context of informed consent procedures [35]. Our primary analysis is an ITS analysis approach. Using an ITS analysis, will allow us to compare the outcome trend (level and/or slope changes) before and after the introduction of the newly developed evidence-based informed consent forms [36].

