#### Statistical model

We will report baseline characteristics of the study population and outcomes descriptively.

We will use an ITS analysis to determine level and slope changes after the implementation of the evidence-based informed consent forms. We will use segmented regression models for our analysis. The basic model is *Y*_*t*_ = *β*_0_ + *β*_1_*T*_*t*_ + *β*_2_*X*_*t*_ + *β*_3_(*T* − *T*_0_)*X*_*t*_

*X*_t_ is a dummy which differentiates pre- and post-intervention periods. *T* is the time since the start of the study in months. β_0_ is the base level. β_1_ is the course of the slope before the implementation of the intervention. β_2_ is the level change, which describes the immediate effect on *Y* after the implementation of intervention *X*. β_3_ is the course of the slope after the implementation of the intervention, whereby *T*_o_ is the time of beginning of the study. We will use negative-binomial regression models for all count data (nocebo effect and objective knowledge questions) and generalized linear model for outcomes which can be analyzed as continuous variables (anxiety, satisfaction, quality of life, OKS).

We will create two models. One model will analyze the intervention as a complex package of measures on hospital level. The intervention effect will be analyzed on the hospital level. We will adjust the analysis for potential unforeseen time-varying confounders (e.g., changes of the standard consent form by hospital information policies, structural changes in consent because of corona pandemic). Potential confounders for each outcome will be identified based on visual inspection of trajectory curve and content-related thinking. We will assess autocorrelation by examining the plot of residuals.

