In a second model, we will analyze the intervention effect on an individual level. This means, the study is analyzed as historical cohort study. In this model, the individual intervention components (informed consent forms, parallel performance of informed consent by orthopedic and aesthetic medical staff, participation on the training for evidence-based decision-making) are modelled as separate intervention components. We will perform this exploratory analysis to get insights into the isolated effect of evidence-based informed consent forms and interaction effects with other intervention components. We will adjust the models for baseline characteristics (age, sex, educational level, and marital status) and a potential time trend (since the comparison group is a historical control).

In case > 5% of data for an outcome are missing, we will impute the missing data by multiple imputation using the Markov chain Monte Carlo method. In addition to this primary analysis, we will perform a best-case/worst-case analysis to assess the robustness of results depending on missing data [48].

To quantify the statistical uncertainty, the associated 95% confidence intervals will be provided for all effect estimates. As we will conduct an explorative pilot study, we will not perform a test for statistically significant differences. We will prepare interrupted-time-series graphs to visualize the results [49].

All analyses will be performed using SAS software [50] and R [51].

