## Limitations

The study was planned as a non-randomized study and is therefore at risk for confounding bias. Moreover, this is a time series study which might be biased by temporal effects. The risk of temporal changes is in particular high because of the dynamic COVID-19 pandemic (e.g., hospital limits surgery to patients with acute pain). A randomized controlled trial would control for unmeasured confounding. However, we decided against a randomization on individual level because we anticipated that there is a high risk of bias due to contamination. The study was not planned as a cluster-randomized trial because this would have exaggerated the expense for a pilot-trial.

Finally, external validity might be limited because the study is only performed in one hospital in Germany.

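### The primary package-effect model neither names nor prespecifies adjustment for patient mix, although the protocol foresees that the mix may change

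*Protocol article*

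**What the plan says.** In the protocol article, the section on sub-study III makes the interrupted time series primary: "Our primary analysis is an ITS analysis approach". The Statistical model section then describes two models.

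- **First model.** "One model will analyze the intervention as a complex package of measures on hospital level". Its adjustment clause reads: "We will adjust the analysis for potential unforeseen time-varying confounders". The two examples given are a change in the hospital's policy on the standard form and a change in how consent is organised, the latter linked to the pandemic. No patient characteristic is named. On selection: "Potential confounders for each outcome will be identified based on visual inspection of trajectory curve and content-related thinking".
- **Second model.** This is an individual-level analysis, described as a historical cohort and as exploratory. It models the forms, the joint consent procedure and the training as separate components. Only here are patient covariates fixed: "We will adjust the models for baseline characteristics (age, sex, educational level, and marital status) and a potential time trend".

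The same section also promises: "We will report baseline characteristics of the study population and outcomes descriptively". It does not say whether this will be by phase or by month.

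The Limitations section states: "The risk of temporal changes is in particular high because of the dynamic COVID-19 pandemic (e.g., hospital limits surgery to patients with acute pain"). Table 1 schedules patient characteristics and baseline anxiety at enrolment, about four weeks before surgery. Pain and function are scheduled only at 30 days after discharge.

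**The concern.** The study has one hospital and no control series. The estimated level change compares the outcome just after the switch with the pre-phase trend carried forward to it, so months close to the switch carry much of the weight. A linear trend absorbs slow drift in the kind of patient treated. It does not absorb a disturbance of a few months that ends at the switch, or a step that coincides with it.

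The protocol's own example of temporal change, surgery limited to patients with acute pain, is such a disturbance. If it ended when the new forms arrived, and those patients were more anxious, anxiety would appear to fall because of the package. Nothing fixed in advance for the package effect would remove or reveal this, because the patient covariates belong to a model that estimates something else, namely component effects.

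The stakes are those of a pilot, but they are real. Under Sample size, the pilot is to supply the basis for planning a definitive trial. Under Discussion and practical implications, indications of positive effects lead to that trial. A biased level change feeds both, and its confidence interval does not show the bias.

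**Working it through.** **The plan's own figures.** The protocol gives no figure on patient mix. Its sample-size figures, which supply the n used here, reproduce: 220 × 0.90 = 198, and 1 − 0.98^198 = 0.982 against the stated 98%.

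**Inputs from the protocol**
- 12 months pre and 12 months post (Recruitment).
- 198 analysed, so 198 / 24 = 8.25 patients per month.
- Segmented regression with intercept, trend, level change and slope change (Statistical model).

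**Assumptions for the check**
- 24 monthly points, equally weighted and independent.
- The post-phase time term is centred at the switch (12.5). The text defines T₀ as the start of the study. That changes what β₂ alone means, but not the fitted lines or the gap between them at the switch, which is the quantity examined here.

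**Step 1: how much of a mix shift enters the level change.** With design matrix M, the level change is the corresponding row of (MᵀM)⁻¹Mᵀ applied to the monthly series. Applying that row to a shift of size 1 gives:

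| Shift in the monthly mean | Share entering the level change |
|---|---|
| Last 2 pre-months only | −0.586 |
| Last 3 pre-months only | −0.816 |
| Last 4 pre-months only | −1.005 |
| Lasting step exactly at the switch | 1.000 |

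For three months, centring at 12 or 13 gives −0.77 or −0.86, so the choice matters little.

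Shifts away from the switch matter much less. With centring at 12, a lasting step 1, 2, 3 or 4 months early enters at 0.71, 0.45, 0.23 and 0.05. A step 1, 2 or 3 months late enters at 0.67, 0.38 and 0.14. A temporary shift in months 4 to 6 enters at −0.08. The slope terms take up part of these shifts.

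The two patterns agree with each other: a rise three months early (0.23) that reverses at the switch (−1.00) gives 0.23 − 1.00 = −0.77.

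**Step 2: precision.** With the outcome in SD units and 8.25 patients per month, the standard error of the level change is 0.285 SD.

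**Step 3: size in outcome units (assumed inputs, not in the protocol).**
- *Temporary restriction.* The share of severe-pain patients rises from 30% to 60% in the last three pre-months, and they are 0.6 SD more anxious. The shift in the monthly mean is 0.30 × 0.6 = 0.18 SD. The false level change is −0.816 × 0.18 = −0.147 SD, which is 0.147 / 0.285 = 0.52 standard errors. A simulation with 198 patients and no true effect gave −0.150.
- *Step at the switch, on the 0–10 scale.* A mix change of 10 to 30 percentage points times an outcome difference of 1 to 3 points gives 0.10 × 1 = 0.1 to 0.30 × 3 = 0.9 points.

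**Step 4: what adjustment can achieve.** In the simulation of the temporary restriction, the level change fell to −0.004 once the severe-pain indicator itself was in a patient-level segmented model. Table 1 schedules no such variable before surgery. The four listed covariates would remove the bias only as far as they track pain severity.

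**The case against.** A reader might infer that no planned analysis adjusts for or checks patient mix at all. The text does not support that. The first model's confounder clause is open-ended and could take in a pandemic restriction on surgery. Baseline characteristics will be described. The second model is adjusted for four patient characteristics and a time trend. What remains is narrower: for the package effect, patient mix is neither named nor fixed in advance, and what to adjust for is decided per outcome after the curves have been seen.

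A reader might also infer that the new forms themselves would be credited wrongly. The first model estimates the whole package, so the error would be a false package effect.

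Three further objections carry weight:

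- **Size.** The bias is substantial only for shifts close to the switch, and the worked example places an assumed doubling of severe-pain patients there. Even so it is about half a standard error. This stands.
- **Context.** This is an exploratory pilot with confidence intervals and no tests, and it declares its confounding risk. The consequence is a biased pilot estimate, not a false confirmatory claim. This stands, but declaring a risk does not reduce it when data that could partly reveal it are already collected.
- **Detail left to the analysis plan.** Exact covariate lists and supplementary checks often sit there. Here, however, the article itself assigns patient covariates to one model, not the other, and names the threat that makes the difference matter.

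Enrolment anxiety is not automatically a variable that the forms cannot influence. According to Participant timeline, the anesthesia consent may also take place about four weeks before surgery, and the order relative to the baseline anxiety measurement is not stated.

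**Conclusion.** The point holds in a limited form. The protocol foresees a change in who is operated on, but its primary package-effect model does not name or prespecify adjustment for it; patient covariates are fixed only for the exploratory component model. A shift in the last two to four pre-months enters the level change at 0.59 to 1.00 of its size, and a step at the switch enters in full. Both would be read as package effects. These shares follow from the 12+12 month design, given equally weighted, independent monthly points.

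The size in outcome units, about 0.15 SD or 0.1 to 0.9 points on the 0–10 scale, rests wholly on assumed inputs. A reader might take the simulated fall to about zero as the expected benefit of adjusting for the listed covariates. It is not, since that result needs a pre-operative pain variable that Table 1 does not list. The change is worth making because it costs little and improves on the stated method.

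**What to change.** 1. Keep the unadjusted monthly series. Beside it, prespecify a patient-level segmented regression with the same level and slope terms for the whole package, adjusted for age, sex, educational level and marital status. Add baseline anxiety for patients in whom it was measured before any consent form was given, and state how that order is recorded.
2. Plot these enrolment characteristics by month and fit the same segmented model to them. Report estimates with 95% confidence intervals as a descriptive check, without a pass/fail rule, in keeping with the plan not to test.
3. If they shift at the switch, report the outcome level change with an explicit caveat that patient mix may explain part of it.
4. Name patient mix in the first model's confounder clause.

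**Cost.** Analysis work and a few degrees of freedom; the covariates are already scheduled for collection. The check is imprecise: with a standard error of about 0.285 SD, its 95% interval is roughly ±1.96 × 0.285 = ±0.56 SD, so an unremarkable result does not rule out a relevant shift. Control is partial for want of a pre-operative pain measure, and the report should say so.

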#### Blinding

Standard consent forms and evidence-based informed consent forms are obviously different. Therefore, blinding of medical staff will be impossible. We will not explicitly inform participants about receiving a “different” informed consent form but only about the nature of the study. The statistical analysis will be performed blinded.

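### Confounders for the primary interrupted time series model are chosen outcome by outcome, partly from that outcome's own curve, so its nominal 95% intervals can cover too little

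*Protocol article*

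**What the plan says.** The opening of Sub-study III names the interrupted time series analysis as the primary analysis. Under Statistical model, the hospital-level version is a segmented regression in which X "is a dummy which differentiates pre- and post-intervention periods" and T "is the time since the start of the study in months". On adjustment it says "We will adjust the analysis for potential unforeseen time-varying confounders", with two examples: changes to the standard consent form through hospital policy, and pandemic-related changes to the consent process. The selection rule is "Potential confounders for each outcome will be identified based on visual inspection of trajectory curve and content-related thinking". On serial dependence the article says only "We will assess autocorrelation by examining the plot of residuals".

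Uncertainty is expressed through intervals alone: "the associated 95% confidence intervals will be provided for all effect estimates", and "As we will conduct an explorative pilot study, we will not perform a test for statistically significant differences". The Blinding section adds, without describing a mechanism, "The statistical analysis will be performed blinded".

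The second, individual-level model has a named covariate set (age, sex, education, marital status and a time trend). The selection rule does not touch it.

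**The concern.** A confounder picked because it matches a visible dip or peak in the outcome has been picked using the outcome. The interval for the level change is then computed as if that covariate had been fixed in advance, so it omits the variability introduced by the choice. With few and noisy monthly points, some dips and peaks will be chance. Choosing separately for each outcome also allows one hospital event to be adjusted for in one outcome and ignored in another because of how the curves look.

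No tests are planned, so this is not a type I error claim. The intervals are the stated expression of uncertainty. The Discussion makes a definitive cluster-randomized trial depend on this pilot pointing to positive effects, and the Sample size section says the pilot will supply the basis for sizing that trial. A level change created, removed or made to look too precise by adjustment would feed into both decisions.

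**Working it through.** **Inputs from the article.** Recruitment: 12 months pre and 12 months post, so about 24 monthly points. Sample size: 220 planned, 10% dropout, 220 × 0.9 = 198 analysed, and 198/24 = 8.25 per month.

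**The plan's own figure.** The chance of seeing at least once a problem of 2% frequency among 198 participants is 1 − 0.98^198 = 0.9817. This reproduces the stated 98%. It is not in dispute and has no bearing on interval coverage.

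**Assumptions, since the article gives no values.** Normal monthly means, a true effect of zero and no real external shock. The model has an intercept, T, X and (T − change-over)·X, fitted by least squares with nominal 95% t-intervals. Post-period time is counted from the change-over so that β2 is the level change. Errors are independent or AR(1) with lag-1 correlation ρ. There are 4,000 runs per cell, so the Monte Carlo standard error at 81% coverage is √(0.81 × 0.19/4000) = 0.6 points.

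**Three selection rules.** (a) No added term. (b) The best of four 3-month windows fixed beforehand, kept if |t| > 2. (c) The best-fitting window of 2–6 months anywhere in the series, kept if |t| > 2. Rule (b) stands for choice limited by content; rule (c) for choice driven by the curve alone.

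Coverage, level change / slope change:

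| ρ | (a) fixed model | (b) few fixed windows | (c) free choice |
|---|---|---|---|
| −0.2 | 97.8% / 98.2% | 96.3% / 96.6% | 86.0% / 85.2% |
| 0 | 94.8% / 94.9% | 93.4% / 93.9% | 80.7% / 76.4% |
| 0.2 | 90.4% / 88.7% | 88.7% / 87.4% | 76.6% / 70.6% |
| 0.3 | 87.4% / 84.8% | 86.0% / 82.7% | 75.8% / 67.6% |

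With independent errors, rule (c) kept a window in 93% of runs although no shock existed; rule (b) did so in 22%.

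**Sensitivity to the selection rule (independent errors, level change).** Always adding one freely chosen 2–4-month window gave 83.0% (8,000 runs). A further simulation gave about 85% for free choice, 92% with 8 candidate windows and 93% with 3. Selection alone therefore costs 94.8 − 93.4 = 1.4 points with few content-based windows, and about 10 (95 − 85) to 14 (94.8 − 80.7) points with one free choice.

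**Autocorrelation.** The approximate 95% band for a lag-1 correlation from 24 points is ±1.96/√24 = ±0.40, so a plot can easily miss 0.2–0.3. How large ρ might be follows from φ·ICC/[ICC + (1 − ICC)/8.25], where ICC is the between-month intraclass correlation and φ the correlation of successive month effects:
- ICC 0.01, φ 0.5: 0.005/(0.01 + 0.12) = 0.04
- ICC 0.05, φ 0.8: 0.04/(0.05 + 0.115) = 0.24

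Both ICC and φ are assumed ranges.

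**Blinding.** The model needs T in months and the pre/post dummy X, and the Interventions section sets the change-over at a pre-specified time. Phase is a function of date, so anyone inspecting the trajectory against time can infer it. Hiding labels does not separate the choice of confounders from the outcome.

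**The case against.** The rule has two parts, and the second, subject-matter reasoning, is a real limit. The article's examples are events that can be verified outside the data. If only a handful of such events are ever considered, the loss is one or two points. The low-80s figures describe a choice with no link to any event, which is not the rule as written. This stands, and it is why the result is a range. The limit may be loose in practice: recruitment was planned for March 2021 to February 2023, and the Limitations section itself calls the risk of temporal change high because of the pandemic, so a plausible event may be found for many dips.

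A reader might infer that the intervals will come from a model assuming independence. The article does not say so. It names a plot and is silent on what follows, and the response may sit in an analysis plan not shown. A reader might also take the blinding sentence as a promise that confounder selection is protected. It promises no such thing; the point is only that blinding cannot supply that protection.

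It is also fair that real shocks should be adjusted for, that unforeseen events cannot be listed at protocol stage, and that this is an explorative pilot with planned graphs and published anonymized data, so readers could check the adjustments. Yet an unforeseen event can be logged when it happens, without sight of outcomes.

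Finally, the simulations are Gaussian, whereas the nocebo and knowledge outcomes are assigned negative-binomial models. The figures are illustrative for those outcomes.

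**Conclusion.** The concern holds as a risk written into the stated rule. Letting each outcome's curve help to select its confounders means that nominal 95% intervals for the level change can under-cover: about 93% with a few content-based windows, down to about 81–85% when one window is chosen freely from the curve. These figures assume 24 independent Gaussian monthly points, no true effect and no real shock.

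It would be tempting to say that the intervals will under-cover. The documents do not support that: the outcome depends on how tightly content limits the choice, and negative autocorrelation can push coverage of a fixed model above 95%.

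Autocorrelation is secondary. If uncorrected in an otherwise fixed model, level-change coverage is about 90% at ρ = 0.2 and 87–88% at 0.3, but the true value is unknown and may be small. The change should be made, though it does not invalidate the pilot, and the individual-level model is unaffected.

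**What to change.** - Keep a dated log of external events (consent-form changes, pandemic restrictions, staffing) from hospital records, made without reference to outcome data.
- Before any outcome curve is opened, lock the confounders for each outcome on content grounds. The lists may differ between outcomes if justified in advance: outcomes are measured at different times, and unneeded terms are costly with 24 points.
- Report the model without these adjustments alongside the adjusted one, and label any adjustment prompted by a curve as a sensitivity analysis.
- State in advance an autocorrelation-adjusted method for the primary intervals, whatever the residual plot shows: for example AR(1) by restricted maximum likelihood, or a Newey–West variance with small-sample correction. Keep the plot as a diagnostic.
- Say what the blinding of the analysis consists of in a time series, or replace the sentence with a commitment to lock the analysis code on dummy data.

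The cost is wording, a simple log and code. The intervals may become somewhat wider.

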#### Interventions

We include two groups of participants before (pre) and after (post) the introduction of the intervention. The group in the pre period (control group) will give informed consent based on standard consent forms from the Thieme-compliance publisher (https://shop.thieme-compliance.de/patientenaufklaerung/thieme/de/Artikel/Aufkl%C3%A4rungsb%C3%B6gen/c/00000), which represents routine care in the study center. The group in the post-period (intervention group) will give informed consent based on our newly developed evidence-based informed consent forms (see sub-study II). The change of the informed consent forms will be introduced at a pre-specified time-point. The informed consent procedures for surgery and for anesthesia will be performed together as far as feasible in the usual hospital workflow.

In addition, physicians performing informed consent in the post-phase will be offered a training in evidence-based decision-making to adequately implement the evidence-based informed consent forms. The training will be based on the basic curriculum for evidence-based decision-making, developed by the *German Network for Evidence-based Medicine*. A curriculum-based, blended learning training program for physicians and medical students has already been developed and pilot tested [37]. This training will be converted to an e-learning module to be independent of possible restriction due to the COVID-19 pandemic. In addition, e-learning with only short phases of virtual presence offers more flexibility. The training will also be adapted to address evidence-based decision-making on TKA. For major changes pilot testing will be considered.

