### Participant timeline

Table 1 depicts the participant timeline. The study includes a pre-interruption and post-interruption-phase. Participants in the pre-phase will receive informed consent based on standard consent forms (control) while participants in the post-phase will receive informed consent based on the newly developed evidence-based consent forms (intervention). Irrespective of the phase, all participating patients will follow the same study flow: study enrollment of each patient will take place approximately 4 weeks before surgery. They will receive informed consent procedures for TKA approximately 2–4 days before surgery. The informed consent procedure for anesthesia takes place approximately 4 weeks or 2–4 days before surgery, depending on the patients’ morbidity and the flexibility in scheduling. Outcomes will be measured at four specific time points for each patient: at the day of enrollment, 1 day before surgery, 3 days and 30 days after discharge from hospital.

**Table 1 Tab1:** Participant timeline (SPIRIT figure)

	Study period (25 months)													
		Pre-phase						Interruption	Post-phase					
	Time-point	4 weeks before surgery	2–4 days before surgery	1 day before surgery	Surgery	3 days after discharge	30 days after discharge		4 weeks before surgery	2–4 day before surgery	1 day before surgery	Surgery	3 days after discharge	30 days after discharge
**Enrolment**	**Eligibility screen**	X							X					
	**Informed consent**	X							X					
**Control**	**Standard consent form anesthesia**	X^a^	X^a^											
	**Standard consent form TKA**		X											
**Intervention**	**Evidence-based consent form anesthesia**								X^a^	X^a^				
	**Evidence-based consent form TKA**									X				
	**Surgery**				X							X		
**Assessments**	**Patient characteristics**	X							X					
	**Baseline anxiety**	X							X					
	**Anxiety**			X							X			
	**Health knowledge**			X							X			
	**Satisfaction with physician-patient-communication**			X							X			
	**Nocebo-effect**					X							X	
	**Quality of Life**						X							X
	**Pain and function**						X							X

^a^Informed consent for anesthesia takes place approximately 4 weeks or 2–4 days before surgery, depending on the patients’ morbidity and the flexibility in scheduling

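### In the exploratory component model, the joint-consent coefficient partly carries the timing of the anesthesia consent, because joint consent is possible only at the 2–4 day visit and timing is not adjusted for

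*Protocol article*

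**What the plan says.** All references are to the protocol article, Sub-study III unless stated.

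- **Statistical model.** The second model works at the level of the individual patient. The forms, the training and "parallel performance of informed consent by orthopedic and aesthetic medical staff" (read here as orthopedic and anesthetic staff) "are modelled as separate intervention components". The analysis is labelled exploratory. Its purpose is to learn what the forms do on their own and how they interact with the other components.
- **Adjustment, same section.** "We will adjust the models for baseline characteristics (age, sex, educational level, and marital status) and a potential time trend". Neither morbidity nor the timing of the anesthesia consent is listed.
- **Participant timeline and Table 1, TKA consent.** "They will receive informed consent procedures for TKA approximately 2–4 days before surgery". This is the only slot.
- **Participant timeline and Table 1, anesthesia consent.** It "takes place approximately 4 weeks or 2–4 days before surgery, depending on the patients’ morbidity and the flexibility in scheduling".
- **Interventions.** The two consent procedures "will be performed together as far as feasible in the usual hospital workflow", so joint consent will vary between patients.
- **Outcome times.** Surveys take place "at the day of enrollment, 1 day before surgery, 3 days and 30 days after discharge from hospital". Table 1 puts anxiety, knowledge and satisfaction at the survey on the day before surgery.

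**The concern.** The two consents share only one slot, 2–4 days before surgery. Joint consent therefore implies recent anesthesia consent, while its absence covers two kinds of patient: those consented separately but recently, and those consented for anesthesia about four weeks earlier. A model with a joint-consent term and no timing term contrasts the joint patients with that mixture.

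Two things differ between early and late anesthesia consent. The first is recency: how long before the survey the patient read the anesthesia form. This is most plausibly relevant to anxiety, knowledge and satisfaction. The second is case mix, since the protocol says timing depends on morbidity. That could also matter for patient-reported adverse events, quality of life and the Oxford Knee Score. The four listed baseline characteristics and a calendar-time trend do not describe an interval that is set patient by patient.

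The stake is attribution. Part of a timing effect could be reported as an effect of joint consent, or as an interaction between form and joint consent, in the model meant to separate the components.

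**Working it through.** **The protocol's own figures.** The Sample size section gives 220 × 0.9 = 198 analysed, and 1 − 0.98^198 = 0.982, which matches the stated 98%. The point does not depend on these; 198 is used below only for precision.

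**Intervals to the survey on the day before surgery.** Anesthesia consent at 2–4 days: 2 − 1 = 1 to 4 − 1 = 3 days. Anesthesia consent at about 4 weeks: 28 − 1 = about 27 days.

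**Share of a timing effect absorbed.** Let e be the share of patients with anesthesia consent at 4 weeks and j the share with joint consent among the rest. The documents give neither. In a linear model without a timing term, the joint coefficient gains

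(timing effect) × [P(late | joint) − P(late | not joint)].

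On the scheduled slots P(late | joint) = 1, so the bracket equals the share of early patients in the non-joint group:

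s = e / (e + (1 − e)(1 − j)).

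| Assumed e | Assumed j | s |
|---|---|---|
| 0.1 | 0.3 | 0.10/0.73 = 14% |
| 0.2 | 0.5 | 0.20/0.60 = 33% |
| 0.4 | 0.7 | 0.40/0.58 = 69% |
| 0.5 | 0.6 | 0.50/0.70 = 71% |
| 0.6 | 0.9 | 0.60/0.64 = 94% |
| 0.7 | 0.9 | 0.70/0.73 = 96% |

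A simulated linear regression at e = 0.5, j = 0.6, with no true joint effect and a timing effect of 1, gave a joint coefficient of 0.72 without the timing term and 0.00 with it. For the outcomes planned as negative-binomial models, the same mechanism applies but the formula is only approximate.

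**Interaction.** Within each period the joint contrast gains s × (timing effect). The form-by-joint interaction gains the difference between the post and pre values of that product. It is therefore affected only if the timing effect differs by form, or if s changes between periods and the timing effect is not zero.

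**Illustration in SD units.** If the timing effect were 0.3 SD, which is an assumption with no source in the documents, the joint coefficient would gain 0.3 × 0.33 = 0.10 SD (20%/50%), 0.3 × 0.69 = 0.21 SD (40%/70%) or 0.3 × 0.94 = 0.28 SD (60%/90%). If the timing effect is zero, all three are zero.

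**Precision at 40%/70%, n = 198, other covariates ignored.**

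- Share joint = 0.6 × 0.7 = 0.42, or 83 joint and 115 not joint.
- Unadjusted SE = √(1/83.2 + 1/114.8) = 0.144 SD; 95% half-width 1.96 × 0.144 = 0.28 SD.
- Squared correlation of joint and late = 0.168² / (0.42 × 0.58 × 0.6 × 0.4) = 0.483, where 0.168 = 0.42 − 0.42 × 0.6. Variance inflation = 1/(1 − 0.483) = 1.93.
- Half-width with the timing term = 0.28 × √1.93 = 0.39 SD.
- Restricting to late patients instead leaves 83 joint and 198 × 0.6 × 0.3 = 36 non-joint. SE = √(1/83.2 + 1/35.6) = 0.200 SD, half-width again 0.39 SD.

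Over e = 0.1 to 0.7 and j = 0.3 to 0.9, the variance inflation runs from 1.04 to 7.3.

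**The case against.** **The model is exploratory.** No significance tests are planned, and the hospital-level interrupted time series analysis does not contain this term. This stands, and it limits the point to how the component model is read.

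**The main interest is the form effect.** The form coefficient is essentially the pre/post contrast. Omitting timing would disturb it mainly if timing or joint consent shifted between periods, which nothing in the documents shows. This stands too. A reader might infer that the isolated form effect or the primary analysis is biased; the documents do not support that.

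**Recency may be part of what joint consent delivers.** In routine care, making a 4-week patient joint would mean a later anesthesia consent, so the unadjusted coefficient could be defended as pragmatic. This does not defeat the point. Timing is settled by morbidity and scheduling before joint consent becomes possible, and the stated aim is to separate the components.

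**The size is assumed.** A reader might take 0.10–0.28 SD as the bias. That range holds a 0.3 SD timing effect fixed, so it excludes zero by construction. All patients have TKA consent at 2–4 days, and the outcomes are not confined to anesthesia, which argues for a smaller shift on whole scores. At 40%/70% the illustrative 0.21 SD also lies inside the unadjusted half-width of 0.28 SD. This stands: only the share absorbed can be derived, and only for assumed e and j.

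**Covariates of a secondary model are usually left to the analysis plan.** That is often so, but here the article itself fixes both the components and the adjustment list.

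**Conclusion.** The point holds as a minor matter of interpretation. On the protocol's own schedule, joint consent occurs only with anesthesia consent at 2–4 days, and the stated adjustment list contains neither that timing nor morbidity. The joint-consent coefficient therefore takes up a share of any timing effect: 69% at the assumed 40%/70%, and 14% to 96% over the wider assumed ranges. An interaction with the form is exposed under the conditions shown above.

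The confounding is partial. Patients consented separately but both times at 2–4 days allow joint consent and timing to be told apart once timing is in the model. The conclusion assumes the scheduled slots are broadly kept. They are given as approximate, but no other shared slot is described.

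**What to change.** In the Statistical model section, add one indicator for the timing of the anesthesia consent (about 4 weeks versus 2–4 days before surgery) to the individual-level model. Restricting the joint-consent contrast to patients with anesthesia consent at 2–4 days is an alternative or a sensitivity analysis, not an additional step, because the indicator is constant in that subset. The indicator handles timing and any case mix that acts through it. Report e and j by period so that readers can judge the overlap.

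In Sub-study IV, make sure that the standardized form documenting the consent process captures the date of the anesthesia consent. The examples listed there include whether orthopedist and anesthetist acted together but not that date; the list is illustrative, so the field may already exist.

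The cost is one recorded field and a wider interval for the joint-consent coefficient: half-width about 0.39 instead of 0.28 SD in the 40%/70% case. A form-by-joint interaction would rest on about 36 late, non-joint patients, roughly 18 per period if evenly split, and should be described as imprecise. Clinical scheduling stays unchanged.
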